### Interim analyses {21b}

There are no interim analyses planned. If less than 10 schools would have been recruited within 1 year, the evaluation study must have been stopped due to insufficient sample size and poor attractiveness of the program. However, this number of schools has already been achieved within the first 6 months of recruitment.

### Methods for additional analyses (e.g. subgroup analyses) {20b}

We plan subgroup analyses for gender (boys, girls), school type (primary school, A-level, B-level), and grade groups (grades 3–4, 5–6, 7–9). Furthermore, the influence of school size and the baseline level of bullying victimization on the effectiveness of *Bullying&You* are planned to be analysed.

### Methods in analysis to handle protocol non-adherence and any statistical methods to handle missing data {20c}

The analysis is an intention to treat analysis; whole schools were randomly assigned to the two conditions intervention group vs. control group. In order to enable sub-analyses differentiated by program dose, a score based on the intensity of the central program components will be created for each school.

Sensitivity analyses are done on the complete-case sample, i.e. excluding schools where measurement points are missing.

To deal with our fourth objective (individual characteristics predicting the program success at the individual level), the association of questionnaires from different time points to pupils is required. Therefore, individual codes with a Levenshtein distance not greater than 2 are assigned to the same pupil. Apart from this strategy to reduce missings, no missing data is imputed.

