**Fig. 2 Fig2:**
[figure not shown]
Bullying&You organization model on target groups and program components (analogue and digital)

**Table 1 Tab1:** Analogue and digital components of Bullying&You

Analogue components	Digital components
**Core team** A group of teachers and social workers serves as their school’s steering group. The core team organizes the implementation of the program components and adapts them to the needs of the school. Core team members receive 3 days of training and are supported by the research team	**ELearning** Pupils (grades 5–9) and teachers work on eLearning units in order to build up knowledge and skills in a flexible and self-determined manner
**Kick-off** The program opens with a 1-h talk for the teachers on the topic of bullying. Further, the results of the school’s first survey and the first steps in the program are presented	**Digital mailbox** Pupils (grades 5–9) and parents report experienced or observed bullying incidents to a school-specific email address. The mailbox is looked after by the core team
**Practical lesson** Once per school year, the core team leads a training for the teachers to deepen and practise the intervention concept in small groups using roleplays	**Digital forums and bulletin board** Forums and a bulletin board enable exchange within and across schools
**Pedagogical day** Optionally, the research team organizes a pedagogical day for the school staff on a selection of topics related to bullying	**Survey** Anonymous pupil surveys are carried out regularly to closely monitor bullying and mental health at school
**Concept for bullying intervention** On-the-spot intervention (i.e. all teachers intervene in the event of inappropriate behaviour) leads to follow-up care (i.e. class teachers follow-up on the bullying incident in conversations with the involved pupils)	
**Concept for break supervision** Bullying during breaks is counteracted by optimizing break organization and supervision, creating offers for activities, and restructuring the schoolyard	
**Class meetings** Class teachers lead pre-designed class meetings in which the pupils are made aware of the topic of bullying and acquire options for action. The focus here is on practical experience and exchange	
**Project day** Optionally, class teachers carry out a pre-designed project day on the topic of team building	

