### Criteria for discontinuing or modifying allocated interventions {11b}

Schools participate voluntarily in the program *Bullying&You* and are free to discontinue program implementation at any time. Pupils are free to leave the CRT (research study) at any time, for any reason, without any consequences. From the investigators’ side, there are no general criteria for discontinuing the intervention. Modification of the intervention may occur based on the continuous exchange with and feedback from the core teams regarding barriers that they come across during program implementation. For instance, some schools may not be able to provide the digital requirements for their pupils to complete the eLearning component of *Bullying&You*. In this case, these schools may entirely omit the eLearning for their pupils or the pupils may follow along the eLearning led by their teacher in class instead of completing it by themselves. To track these modifications, program fidelity of each school will be assessed by short teacher surveys at T1 and T2.

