### Sample size {14}

To estimate the required sample size, Monte Carlo simulations were carried out using Stata 16.1 with the following assumptions: Two measurement points of 15 secondary schools per group with 10 classes per school and 5 primary schools per group with 4 classes per school are expected to take part in the study. In each class, 25 pupils are expected. Baseline bullying prevalence is estimated to be 15%, and the intervention is expected to lead to a relative reduction in bullying of 25%. The standard deviation (*SD*) of bullying rates between schools is *SD* = 0.2 on the logit scale; the *SD* of classes within schools is *SD* = 0.4 on the logit scale. This leads to an intraclass correlation coefficient on the school level of 0.011 and 0.057 on the class level. The assumptions were chosen so that the simulated data corresponded to the data from the OBPP study [18]. With these assumptions, 1000 data sets were simulated and analysed by three-level mixed logistic regression with group, measurement point, and their interaction as fixed effects and random intercepts on the school (level 3) and class (level 2) level. Using an alpha-error probability of 0.05, with 40 schools and 8500 pupils (4250 IG and 4250 CG) the power would be 86%.

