### Plans to promote participant retention and complete follow-up {18b}

Core team members regularly obtain trainings and coordinate and plan the implementation of the program components. This task also comprises the coordination of the baseline and follow-up surveys with their pupils including the coordination of additional assessment dates for previously absent pupils. The research team monitors the progress of the pupil survey and actively contacts the core teams in case of delays or low response rates.

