## Trial status

Recruitment of schools started in September 2021 and was stopped in September 2023. Recruitment of participants began in June 2022 and will be completed by October 2025. The current protocol is version 1 of 2 March 2020. The trial is scheduled to be completed by October 2025.

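### The only stated missing-data check drops schools with a missing measurement point, so it cannot show whether school-level loss has biased the intention-to-treat result, and the plan does not say whether schools that stop the program are still surveyed

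*Protocol article*

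**What the plan says.** Section {20c} describes an intention-to-treat analysis by randomised school. It rules out imputation; the only device against missing data is the matching of near-identical pupil codes. It then gives the sensitivity analysis: "Sensitivity analyses are done on the complete-case sample, i.e. excluding schools where measurement points are missing".

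Three other places bear on how a school's data could go missing:

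- Section {11b}: schools "are free to discontinue program implementation at any time".
- Table 1 lists the survey among the digital components of the program: "Anonymous pupil surveys are carried out regularly to closely monitor bullying and mental health at school".
- Section {18b}, on the duties of the school's core team: "This task also comprises the coordination of the baseline and follow-up surveys with their pupils".

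Section {20a} fits a three-level mixed model with group, measurement point and their interaction, and random effects for school and class. The Abstract names the 1-year follow-up (T1) as the main endpoint.

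**The concern.** A sensitivity analysis for missing data should relax the assumption that the primary analysis makes. Here the primary model takes whatever school data exist, and the stated check then removes every incomplete school. That makes the assumption stricter.

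If intervention schools in which the program was not working were more likely to have no T1 survey, the estimated effect would describe the schools that remained. The label intention to treat would promise more than the data delivered. The complete-case result would tend to agree with the main result, and a reader could take that agreement as evidence of robustness.

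**Working it through.** **1. The plan's own figure.** Section {14} assumes "Two measurement points of 15 secondary schools per group with 10 classes per school and 5 primary schools per group with 4 classes per school", 25 pupils per class, a 15% baseline prevalence, a 25% relative reduction, and logit-scale SDs of 0.2 (schools) and 0.4 (classes). It concludes that "with 40 schools and 8500 pupils (4250 IG and 4250 CG) the power would be 86" per cent.

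- Pupils per arm: 15×10×25 + 5×4×25 = 4250. Classes per arm: 150 + 20 = 170.
- Follow-up rate in the intervention group: 0.75 × 15% = 11.25%. Log odds ratio: logit(0.15) − logit(0.1125) = 0.331.
- Variance of the interaction, with class effects drawn anew at each time point and the school effect shared: 3/(4250×0.15×0.85) + 1/(4250×0.1125×0.8875) + 4×0.16/170 = 0.00554 + 0.00236 + 0.00376 = 0.01166. SE = 0.108.
- Power, two-sided 0.05: Φ(0.331/0.108 − 1.96) = 86.5%. A 4000-run simulation gave 85.2%.

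The stated 86% is reproduced. The 8500 pupils are the full structure of 40 schools, with no allowance for school loss.

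**2. Which schools inform the T1 contrast.**

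| School has data at | Primary model, T1 contrast | Complete-case check, read literally |
|---|---|---|
| T0, T1, T2 | T0 and T1 used | kept |
| T0, T1 | T0 and T1 used | removed |
| T0, T2 | T0 used, nothing at T1 | removed |
| T0 only | T0 used, nothing at T1 | removed |

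In neither analysis does a school without T1 data contribute to the T1 outcome. The check loses the T0 data of such schools. It also loses the T0 and T1 data of a school that misses only T2. The primary model can allow for loss that depends on the bullying level already observed at T0. Neither analysis addresses loss that depends on the unobserved T1 level or on the program's effect in that school.

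**3. Size, under assumptions.** The documents give no discontinuation rate. Assume q of 20 intervention schools have no T1 data, the program has no effect in them, the other intervention schools show the planned 25%, school sizes are equal, and no control school is lost. The intervention rate over all randomised schools is (1 − q/20)×11.25% + (q/20)×15%.

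| q | Rate, all randomised schools | Reduction, all randomised schools | Estimated reduction | Ratio |
|---|---|---|---|---|
| 2 | 11.625% | 22.5% | 25% | 1.11 |
| 3 | 11.8125% | 21.25% | 25% | 1.18 |
| 4 | 12.0% | 20.0% | 25% | 1.25 |

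Using the variance formula of step 1, power with the remaining schools would be 85.5% (q = 2) or 84.2% (q = 4). If all schools were surveyed it would be 77.9% or 67.0%. Under these assumptions the loss would therefore hardly show as reduced power.

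**4. A program with no effect.** Suppose the intervention schools with the worst bullying trend are the ones lost, with an assumed SD of school-level change of 0.1 to 0.3 on the logit scale. The apparent reduction is 1.5% to 4.5% when 2 schools are lost, and 2.8% to 8.3% when 4 are lost. If loss is unrelated to trend and effect, this bias is absent. If it is trend-related in the same way in both arms, it cancels.

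**The case against.** The strongest reply is that stopping the program need not mean leaving the survey. Control schools are surveyed at T0 and T1 without running it. The survey is online and administered in class by teachers ({18a}), and the research team follows up slow or low response ({18b}). Section {11b} also expects some schools to drop components yet remain in the trial. All of this stands. A reader might infer from Table 1 and {18b} that a school which stops necessarily drops out of the survey. The document does not say so, nor does it say that such schools are still surveyed.

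Second, the exclusion of schools applies only to the sensitivity analysis. The primary model keeps all available data by randomised arm. This also stands, so it would be wrong to say that the primary analysis retains mainly the schools that persisted.

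Third, the direction is open. A reader might assume that intervention schools leave because of workload while control schools wait for their turn. Yet {6b} supplies material to control schools specifically to sustain their motivation, so loss there is plausible too.

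A reader might also infer from the timetable ("The trial is scheduled to be completed by October 2025") that primary schools will be removed in bulk for lack of T2. The first primary baselines were in October 2023, so their 24-month survey falls in that final month. Primary schools are also a randomisation stratum, so a calendar cut-off would be roughly balanced by arm.

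Finally, the details of a missing-data analysis usually belong in the analysis plan. That is so, and their absence is not the point here. The article fixes a specific check, and that check cannot do its job.

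**Conclusion.** The point holds in a limited form. Given no imputation, a complete-case check at school level cannot test for informative loss of schools, because it uses the same surviving schools and less of their data. The document leaves open whether schools that stop the program are still surveyed. Taken literally, the exclusion rule also removes a school missing only T2 from the check on the T1 endpoint.

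The possible overstatement is moderate: a factor of 1.11 to 1.25 for 2 to 4 lost intervention schools. On the prevalence scale this is 0.375 to 0.75 percentage points in the intervention rate. It rests on assumed loss, no effect in the lost schools, no T1 data from any of them, and no control loss. Other patterns give no bias or reverse its sign. The change is worth making before the data are analysed, but nothing shows that the primary result will be biased.

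**What to change.** 1. State that every randomised school is asked for the T1 and T2 pupil surveys whether or not it continues the program, and is analysed in its randomised arm. The surveying of control schools at T0 and T1 shows this is workable.
2. Replace or supplement the complete-case check with a sensitivity analysis that keeps all randomised schools. Give an intervention school without T1 the control-group change from T0, meaning no program benefit, and vary that assumption over a tipping-point range. For T2, state the reference explicitly, because control schools will by then have started the program and their change is no longer a no-program change.
3. Judge completeness for the T1 endpoint on T0 and T1 only.

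The cost is a sentence in the school information, a survey link for schools that have stopped, some wording in the analysis plan and one extra model run. Some schools that stop may still refuse the survey, which is why the second change is needed as well as the first.

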### Plans to give access to the full protocol, participant-level data, and statistical code {31c}

The dataset and statistical code can be made available by the corresponding author upon reasonable request.

## Oversight and monitoring

### Composition of the coordinating centre and trial steering committee {5d}

This trial is designed, performed, and coordinated by the *Bullying&You* research team at the Child and Adolescent Psychiatry Department at the University Hospital Heidelberg. Day to day support for the trial is provided by the principle investigator, the study coordinator, and the research assistants. The entire team meets approximately once a month. Additional support is provided by an IT system developer and a data analyst.

### Composition of the data monitoring committee, its role and reporting structure {21a}

We have not established a Data Monitoring Committee (DMC). However, despite the absence of a DMC, we are committed to ensuring scientific and ethical standards. We implement alternative monitoring measures, such as regular reviews of trial progress and monitoring data safety. Additionally, we maintain close collaboration with regulatory authorities and the ethics committee.

### Adverse event reporting and harms {22}

There are no obvious harms for participants of the trial and it has been proven that addressing self-harm behaviour to children and adolescents does not have an iatrogenic effect, but can even have a positive preventive effect—especially in younger participants [45]. Nevertheless, completing the survey could potentially lead to psychological distress for those pupils affected by bullying. In order to cope any strain that may arise, every school appoints a qualified contact person (e.g. social worker, counsellor, or core team member) whom the pupils can consult for support. This contact person is communicated to the pupils at the beginning of the survey. Any serious adverse effects of the study can also be reported to the research team. Furthermore, to prevent harms, everybody can deny participation in the survey as part of the program and/or in the accompanying study at any time without stating the reason and without any individual disadvantage for subsequent school career or medical care.

### Frequency and plans for auditing trial conduct {23}

We do not have a specific audit plan for this trial. However, we acknowledge the importance of monitoring and ensuring the integrity of the trial.

### Plans for communicating important protocol amendments to relevant parties (e.g. trial participants, ethical committees) {25}

The study was appraised and approved by the Ethics Committee of the Medical Faculty at the University of Heidelberg (S-471/2020), as well as of the Ministry of Education of the state of Baden-Wuerttemberg. Furthermore, the study was registered at a WHO trial registry (German Clinical Trials Register, DRKS00028183). In case of relevant protocol modifications, the institutional review board of the Medical Faculty at the University of Heidelberg is informed and an amendment is submitted. Furthermore, information within the German Clinical Trials Register is updated to inform the public about possible changes. In case any amendments concern the participants, they are also informed about the changes.

### Dissemination plans {31a}

To disseminate the results within the scientific community, research publications in peer-reviewed journals and conference contributions are planned. Access to the protocol is ensured through the registration and regular update of the trial in the German Clinical Trials Register. The 40 pilot schools will receive the results of our evaluation study via digital information and events. Depending on the results, information about the program, its effectiveness, and availability (after-study stage) shall be provided to a larger scale of schools, teachers, and other professionals working in the field. Awareness in the general public will be increased by the *Bullying&You* website (www.mobbing-und-du.de) and press campaigns.

## Discussion

Peer relationships play an important role in children’s and adolescents’ lives, and the importance of peer relationships steadily rises with increasing age. Bullying is a man-made, intentional aggression, which is consistent with the defining features of maltreatment or abuse. As a form of peer‑to‑peer maltreatment, bullying implies severe consequences for mental health and academic achievement, mostly for victims [5]. While there is evidence for the overall effectiveness of school-based bullying prevention programs [14], randomized trials are still urgently needed, and further developments of feasible as well as permanently effective programs are critical. There is still a lack of systematic bullying prevention and, therefore, there exists the need for the development of new, innovative research-based programs in Europe to fill this gap [26]. Currently, programs are often only translated or adapted and do not correspond to the needs of the local school system and culture. However, newly developed interventions must be evaluated and, in a second step, improved based on the obtained results. Modern and flexible program components like eLearning units are needed to make anti-bullying programs more feasible and attractive to the pupils and school staff. Additionally, the school staff’s perspective should be included in the development of the program by consulting focus groups and programs should also target primary schools, as the effect of anti-bullying programs proved to be larger for younger children [46].

Therefore, the Child and Adolescent Psychiatry Department at the University Hospital Heidelberg has developed the program *Bullying&You*. This school-based prevention program aims to reduce bullying by teaching pupils and teachers how to identify, stop, and prevent bullying. Using a CRT design on a large-scale sample, the aim of this trial is to investigate the effectiveness of the *Bullying&You* program at 30 secondary and 10 primary schools.

Despite the well-designed trial and the promising anti-bullying intervention, we may also face some barriers. First, some schools might not be able to profit from the various advantages of the digital program components (e.g. eLearning) because they lack the required digital infrastructure. At times, teachers in Germany are also still rather sceptical or feel insecure when dealing with digital media. These challenges can be addressed by offering modifications of the relevant program components, as well as by providing guidelines for, and intuitive designs of, the digital media. Second, interrelations of aspects affecting the program effectiveness are very complex: some program components might only work for certain age groups, certain forms of bullying, or a particular gender. Further, a program component may not be effective on its own, but in combination with others, proves to be successful. Mediators and moderators of preventive programs have scarcely been researched (‘*What works, for whom, and under what circumstances*’, [47], p. 438). Due to this complexity, we will need to analyse our data carefully to draw our conclusions. Third, implementing a whole-school approach may take some time. Thus, changes in bullying and mental health might not yet be significant after only 1 or 2 years of program implementation. As our evaluation study only comprises 3 measurement points (baseline T0; follow-up + 12 months T1; follow-up + 24 months T2), additional follow-up time points are highly desirable to evaluate the long-term effectiveness and sustainability of *Bullying&You*.

### Implications and future impact

As early as more than 10 years ago, Spiel and Strohmeier [48] expressed their growing disappointment about the slow and incomplete application of research results in the field of education. Results of developmental and educational psychology are overlooked due to a lack of structures and resources, clear standards of evidence, failing transfer into practice, and an existing resistance to change. Intensive cooperation between researchers, politicians, administrators, and the media is required in order to change this unsatisfactory situation for the better. We want to contribute to this change by developing an innovative and feasible bullying prevention program based on state-of-the-art scientific findings. The current mental health crisis in children and adolescents [11], the advantages of the school setting for preventive efforts [12], as well as the lack of German-language school-based bullying prevention programs with proven effectiveness [13] clearly increase the need for such a program.

To conclude, bullying deserves a high level of attention and efforts to be successfully identified, stopped, and prevented. Pupils and teachers must acquire knowledge and build up skills to change their behaviour. If the whole school community feels responsible, actively intervenes in bullying situations, and enforces prosocial behaviour, bullying can indeed be reduced in the school setting and beyond (e.g. in the cyberspace). Unfortunately, available school-based anti-bullying programs are limited in their application; systematic bullying prevention is still lacking within the German school system. *Bullying&You* may help to overcome existing barriers and support schools in becoming a safe place for all of their pupils.

